Question 1: Does a 16-week walking program with the wearable robotic exoskeleton induce beneficial changes on musculoskeletal, cardiorespiratory, and endocrine-metabolic health; wheelchair-related functional skills and mobility; and psychosocial outcomes? Hypothesis 1: It is hypothesized that beneficial effects observed during the postintervention and retention measurement times will significantly and meaningfully exceed any changes observed during the control and preintervention measurement times (ie, T_0_ [control measurement time] vs T_1_ [preintervention measurement time] vs T_2_ [postintervention measurement time] vs T_3_ [retention measurement time]).Question 2: What personal factors best determine and predict the beneficial effects of the walking program with the wearable robotic exoskeleton? Hypothesis 2: It is hypothesized that the individuals with the highest level of SCI and the longest time since the SCI (ie, possibly the best determinants and predictors) will be those who respond best to the walking program.Question 3: What program attributes best determine and predict the beneficial effects of the walking program with the wearable robotic exoskeleton? Hypothesis 3: It is hypothesized that the total number of steps taken will be the best determinant and predictor of the measured changes.Question 4: What are the participants’ satisfaction levels with the walking program and the wearable robotic exoskeleton itself, and what are the expectations regarding its future use in the context of a home- or community-based adapted physical activity program? Hypothesis 4: It is hypothesized that WU_SCI_ will (1) express high levels of satisfaction with the walking program using the wearable robotic exoskeleton and with the wearable robotic exoskeleton itself and (2) report on how they envision its future in the context of home- or community-based use to shape the development of an adapted physical activity program in the future.

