## Methods

### Study Design

A prospective, longitudinal, self-controlled interventional study with multiple discrete measurement times will be used to assess outcomes at baseline (ie, preintervention phase), during the intervention, and thereafter (ie, retention phases) (see Figure 2). While this design may contrast with *classic* study designs frequently recommending a separate comparison group to assess efficacy or effectiveness, the use of a separate comparison group was judged as nonideal in the context of this study, based on the challenges linked to the classification and quantification of the severity of SCIs and their heterogeneous consequences [65]. In addition, interventional trials of new technologies document that potential participants are reluctant to participate, refuse to adhere to the requirements of a control group, or withdraw for the most part from a control group [66,67]. To strike an optimal balance between the need to have a control group with the anticipated strong desire of potential participants to engage in the wearable robotic exoskeleton–assisted walking program, while also considering the amount of, and timeline limits linked to, the study’s funding, the study includes a 4-week observation phase prior to the start of the intervention. Since only individuals with a chronic SCI with *stable* overall health status and life habits will be recruited, outcome measures will be assessed at the start and at the end of the 4-week observation phase. These outcome measures will provide data about each participant’s natural variability and will enable us to detect whether the intervention has an effect greater than the underlying natural variability (ie, patient-specific minimal detectable change criteria computed); they will also enable us to test the effects of the intervention (ie, pre- vs postintervention responses). This boosts the ethical acceptability of the project, minimizes the impacts of potential and unmeasured confounding variables, facilitates recruitment, and mitigates the risk of experimental attrition. Lastly, semistructured interviews and an online questionnaire will capture participants’ satisfaction levels and perspectives about the wearable robotic exoskeleton–assisted walking program and the mobility technology in itself (ie, the wearable robotic exoskeleton).

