### Statistics

#### Sample Size Estimation

The sample size estimate was based on a comparison using the variability of the absolute change (ie, mean ±SD) in both body composition and bone mineral density (ie, main outcomes) measured pre- and postintervention in our preliminary study [61] and computed with a computerized sample size calculator [100]. Considering the self-controlled design of the study, a total of 18 participants are required to have an 80% chance of detecting a significant increase at the 5% level in the leg lean body mass (kg) at the tibia measured by DXA from 14.0 to 15.8 ±2 mg/cm^3^ [61]. Likewise, a total of 18 participants are required to have an 80% chance of detecting a significant increase at the 5% level in the bone mineral density (mg/cm^3^) at the tibia measured by pQCT from 466 to 532 ±70 mg/cm^3^ [61]. Considering the dropout rate of 7.1% found during the feasibility study [46], an additional 2 participants were added for a total sample size of 20 participants.

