#### Quantitative and Qualitative Analyses

Descriptive statistics (eg, mean, SD, and 95% confidence interval) will be calculated for data summarizing sociodemographic characteristics as well as clinical and laboratory outcomes collected at the different measurement times. The normality of all data distributions and the absence of outliers will be verified via the Shapiro-Wilk test of normality and the absence of studentized residuals greater than ±3 SDs, respectively. Whenever applicable, the level of significance will be set at *P*≤.05 for all statistical tests and the data will be analyzed using SPSS, version 25.0 (IBM Corp).

For Hypothesis 1, one-way analysis of variance for repeated measures (ie, normally distributed continuous data) or Freidman tests (ie, non-normally distributed continuous or categorical data) with planned comparisons based on the hypothesis and Bonferroni correction will be conducted to detect significant time effects, with a special interest for the preintervention (T_0_ vs T_1_), intervention (T_1_ vs T_2_), and retention (T_2_ vs T_3_) phases. In accordance with the principles of a classic intention-to-treat approach, all participants will be included in the final analyses, regardless of withdrawal, compliance, or unintentional missing data. For missing data, imputation of the mean value for the specific group at the specific assessment time will be used. Per-protocol exploratory analyses will also be performed comparing outcomes for those with walking program compliances of greater than 75% to examine maximum treatment efficacy.

For Hypotheses 2 and 3, Pearson or Spearman correlation coefficients will investigate the strength and direction of the relationships between the overall observed changes ([T_1_–T_2_] / T_1_ × 100) for each personal factor (ie, dependent variable) and the program characteristics (ie, independent variable). Independent variables having reached a critical threshold (*P*≤.25) will then be confronted in a stepwise multiple linear regression analysis to identify the three best predictors for each dependent variable and the coefficient of determination (*R^2^*) of the model. To determine the factors for identifying the best responders to the program, analyses similar to the previous ones will be completed, except that the independent variables will be sociodemographic characteristics, anthropometric parameters, characteristics of the SCI, personal factors, and functional disability.

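### The Bonferroni correction is not limited to claims of benefit, so it makes the control-phase (T0 vs T1) and retention (T2 vs T3) comparisons less able to show drift or loss

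*Protocol article*

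**What the plan says.** Under Quantitative and Qualitative Analyses, Hypothesis 1 is tested by repeated-measures analysis of variance or the Friedman test, followed by comparisons between times: "planned comparisons based on the hypothesis and Bonferroni correction will be conducted to detect significant time effects, with a special interest for the preintervention". That phase is the change from T0 to T1. The same sentence goes on to name two more comparisons, T1 against T2 for the program itself and T2 against T3 for what follows it. The level is P≤.05. The section does not say how many comparisons the correction covers, and it treats the three named phases alike.

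Their roles come from other sections. Objectives (Hypothesis 1) expects that benefits after the program and at retention "will significantly and meaningfully exceed any changes observed during the control and preintervention measurement times". Study Design explains that a 4-week observation phase replaces a separate comparison group and that the T0 and T1 data "will enable us to detect whether the intervention has an effect greater than the underlying natural variability", through a patient-specific minimal detectable change.

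Sample Size Estimation works at the 5% level with no allowance for a correction: "a total of 18 participants are required to have an 80% chance of detecting a significant increase at the 5% level in the leg lean" mass outcome, and likewise 18 for bone mineral density at the tibia. Two participants are added for dropout, giving 20.

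**The concern.** Bonferroni limits the chance of falsely declaring a difference. That is the right protection where a difference is the claim. Among the three named comparisons, only T1 vs T2 claims benefit through a difference. For T0 vs T1 (drift before the program) and T2 vs T3 (loss after it), the result that suits Hypothesis 1 is no difference. A stricter threshold makes those checks easier to pass.

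In a study without a comparison group this matters. A pre-program change that goes unflagged may leave the T1-T2 change credited wholly to walking, and an unflagged loss after T2 may look like retention. Counting the two checks in the family also takes alpha from T1 vs T2, although neither check can itself produce a false claim of benefit.

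**Working it through.** **Inputs from the documents.** Level 5%, power 80%, 18 required and 20 recruited. Lean mass is "measured by DXA from 14.0 to 15.8 ±2 mg/cm^3" (the unit is as printed), so the difference is 1.8, the SD 2 and the ratio 0.90. Bone density is "measured by pQCT from 466 to 532 ±70 mg/cm^3", so 66/70 = 0.943. The estimate is described as "based on a comparison using the variability of the absolute change (ie, mean ±SD) in both body composition and bone mineral density (ie, main outcomes"), which suggests the SD of the pre-post change.

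**Assumptions.** Two-sided tests; three comparisons share the correction, so 0.05/3 = 0.0167; paired t tests for the drift figures. The drift sizes, in SDs of the change, are illustrative and not from the plan.

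**1. The plan's own 18.**
- Two-sample formula, n = 2 × [(1.960 + 0.842) × SD/difference]²: bone density 17.7, so 18, which matches; lean mass 19.4, so 20, two more than stated.
- One-sample formula with the SD as that of the change (no factor 2): 8.8 and 9.7, so 9 and 10; with the exact paired t test, 11 and 12. Neither gives 18.

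The stated figure therefore fits the two-sample formula, while the description fits an SD of change. Both are carried forward.

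**2. Sensitivity of T0 vs T1 and T2 vs T3.** Power comes from the noncentral t distribution with n − 1 degrees of freedom and noncentrality d√n.

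| True change (SD of change) | n | alpha 0.05 | alpha 0.0167 |
|---|---|---|---|
| 0.4 | 20 | 40% | 23% |
| 0.5 | 20 | 56% | 37% |
| 0.3 | 18 | 22% | 11% |
| 0.5 | 18 | 52% | 33% |
| 0.7 | 18 | 80% | 63% |

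The smallest observed change that reaches significance is t/√n. With n = 20 it is 2.093/4.472 = 0.47 SD at 0.05 and 2.625/4.472 = 0.59 SD at 0.0167.

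If all six pairwise comparisons were corrected (0.05/6 = 0.0083), a 0.5 SD change would be detected with 27% power at n = 20 and 23% at n = 18.

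**3. Cost to T1 vs T2.**

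| Reading of the SD | Outcome | n | alpha 0.05 | alpha 0.0167 |
|---|---|---|---|---|
| SD of change, paired t | Lean mass (0.90) | 20 | 97% | 91% |
| SD of change, paired t | Bone density (0.943) | 20 | 98% | 93% |
| SD of change, paired t | Lean mass | 18 | 95% | 86% |
| SD of change, paired t | Bone density | 18 | 97% | 90% |
| Two-sample formula | Lean mass | 18 | 77% | 62% |
| Two-sample formula | Bone density | 18 | 81% | 67% |

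The last two rows use Φ(ratio × √(18/2) − z). For bone density, 0.943 × 3 = 2.83; subtracting 1.960 gives 81% and subtracting 2.394 gives 67%.

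**The case against.** **The family is inferred.** The text gives no divisor, and special interest in three phases does not strictly say that those three share one correction. This stands: three is the natural reading, not a stated fact. A larger family would weaken the two checks further.

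**No sentence says that a non-significant T0-T1 or T2-T3 result will be read as stability or retention.** A reader might infer it from the design, but the documents do not say it. What the text does leave is a test run to detect differences, with no margin or other rule for judging how much drift or loss is excluded.

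**The observation phase has a second use.** The patient-specific minimal detectable change is untouched by Bonferroni. It is a partial safeguard: it addresses individual variability and does not test a shift in the group mean. The planned descriptive statistics summarise outcomes at each time; the section does not commit to an interval for the change between times.

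**One family for all planned contrasts is ordinary, conservative practice, and T2 vs T3 could also show further gain.** This is fair as regards false positives, and for T1 vs T2 the rule errs against a false claim of benefit. It does not answer the loss of sensitivity where the concern is a missed change.

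**Removing the correction does not make the drift check strong.** This stands. Even at 0.05, a 0.5 SD drift is missed almost half the time with 20 participants, which is why the fix relies on intervals rather than on an uncorrected test.

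**Conclusion.** The point holds as a weakness in how the correction is assigned. On the natural reading of three comparisons, it cuts detection of a 0.5 SD drift or loss from 56% to 37% with 20 participants (52% to 33% with 18). The drift size is assumed, and the figures are for paired t tests; those for rank-based follow-up would differ. Even without the correction, these tests are weak evidence of no change.

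A reader might go further and conclude that the correction leaves T1 vs T2 underpowered. The documents do not support that as a flat statement. With the planning SD taken as the SD of change, as the text describes it, power at 0.0167 is 91-93% with 20 participants and 86-90% with 18, above the 80% target. Only under the two-sample formula that reproduces 18 for bone density does it drop, from 81% to 67% (bone density) and from 77% to 62% (lean mass) with 18. The cost to the test of benefit is therefore a range that depends on what the SD is. The loss of sensitivity in the two checks does not depend on it.

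**What to change.** In Quantitative and Qualitative Analyses, under Hypothesis 1:

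- Limit Bonferroni to the comparisons that claim a benefit, and list them with the divisor: T1 vs T2 and, if a benefit at retention is claimed, T3 against a pre-program value.
- Report the T0-T1 and T2-T3 mean changes with unadjusted 95% confidence intervals, beside the T1-T2 change.
- State that a non-significant T0-T1 or T2-T3 result will not be taken as stability or retention, and that the interval shows how much drift or loss is excluded.

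This takes a few sentences and no new data. The downside is small: where nothing has changed, each of the two checks will be flagged by chance about 5% of the time instead of about 1.7%.

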**Methods:**

A total of 20 WU_SCI_, who have had their injuries for more than 18 months, will complete an overground wearable robotic exoskeleton–assisted walking program (34 sessions; 60 min/session) supervised by a physiotherapist over a 16-week period (one to three sessions/week). Data will be collected 1 month prior to the program, at the beginning, and at the end as well as 2 months after completing the program. Assessments will characterize sociodemographic characteristics; anthropometric parameters; sensorimotor impairments; pain; lower extremity range of motion and spasticity; wheelchair abilities; cardiorespiratory fitness; upper extremity strength; bone architecture and mineral density at the femur, tibia, and radius; total and regional body composition; health-related quality of life; and psychological health. Interviews and an online questionnaire will be conducted to measure users’ satisfaction levels and perspectives at the end of the program. Differences across measurement times will be verified using appropriate parametric or nonparametric analyses of variance for repeated measures.

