### Intervention: Overground Wearable Robotic Exoskeleton–Assisted Walking Program

An Ekso GT (Ekso Bionics) wearable robotic exoskeleton, which has been approved by Health Canada, is used in this study (see Figure 1). At T_1_, participants engage in a wearable robotic exoskeleton–assisted overground walking program that encompasses 34 training sessions offered over a 16-week period. The number of training sessions per week progressively increases to safely and efficiently adhere to the overload principle (see Figure 3). The duration of the training program mimics that of a recent study that confirms for the first time an improvement in bone turnover among individuals with a chronic SCI following a 16-week walking program [39]. The frequency of the training program that progresses from one to three sessions per week matches the latest recommendation from the Physical Activity Guidelines for Adults with SCI, including the new conditional recommendation to engage in at least 30 minutes of moderate-to-vigorous intensity aerobic exercise three times per week for cardiometabolic health benefits [68]. All training sessions are supervised by a certified physiotherapist as well as a physiotherapy assistant as needed [46,53]. During each 60-minute training session, participants perform sit-stand transfers and walk with the wearable robotic exoskeleton and a walking aid (ie, rolling walker or forearm crutches). Verbal and tactile feedback are provided by the physiotherapist as needed.

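### The comparisons named for Hypothesis 1 do not match it: none sets the program change against the control-phase change, and none compares T3 with a pre-program value

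*Protocol article*

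**What the plan says.** Under Objectives, Hypothesis 1 reads: "beneficial effects observed during the postintervention and retention measurement times will significantly and meaningfully exceed any changes observed during the control and preintervention measurement times". This is a claim about one change relative to another, made for both T2 and T3.

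Under Study Design, the protocol explains why it has no separate comparison group and what replaces it: "the study includes a 4-week observation phase prior to the start of the intervention". The data from that phase are meant to "detect whether the intervention has an effect greater than the underlying natural variability (ie, patient-specific minimal detectable change criteria computed").

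Under Quantitative and Qualitative Analyses, Hypothesis 1 is to be tested by one-way repeated-measures ANOVA or the Friedman test. In that section, "planned comparisons based on the hypothesis and Bonferroni correction will be conducted to detect significant time effects", and the sentence ends "with a special interest for the preintervention (T_0_ vs T_1_), intervention (T_1_ vs T_2_), and retention (T_2_ vs T_3_) phases". No other contrast is named, and the minimal detectable change is not taken up there.

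The phases differ in length. The control phase lasts 4 weeks, the program consists of "34 training sessions offered over a 16-week period", and the last visit takes place "as well as 2 months after completing the program".

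**The concern.** The T0-T1 phase is the only comparator in this design. Its value depends on the program change being compared with it. The three named pairs test each phase separately against zero. A non-significant first test followed by a significant second one does not show that the second change is larger, because the difference between the two has not been tested.

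The retention part has a separate gap. The hypothesis places T3 against what happened before the program, but T2 vs T3 looks only at what happened after it. That test cannot distinguish a T3 mean well above the pre-program level from one that has drifted most of the way back.

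At stake is the study's main efficacy statement. A report could say that the benefit exceeded natural change when no analysis had made that comparison.

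**Working it through.** **What each named test asks**

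| Named comparison | Null hypothesis | Part of Hypothesis 1 addressed |
|---|---|---|
| T0 vs T1 | control-phase change = 0 | none directly |
| T1 vs T2 | program change = 0 | a change occurred, not that it exceeds the control phase |
| T2 vs T3 | post-program change = 0 | none: no reference to T1 or T0 |

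The hypothesis needs (T2-T1) > (T1-T0) and (T3-T1) > (T1-T0).

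**Inputs from Sample Size Estimation.** 18 participants before the dropout allowance; leg lean mass 14.0 to 15.8 with SD 2, so 1.8/2 = 0.90 SD; tibial bone density 466 to 532 with SD 70, so 66/70 = 0.94 SD. The section describes the SD as that of the pre-post change, and I take it so.

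**The plan's own figure.** The two-group formula 2(1.96 + 0.84)²/d² gives 17.66, so 18, for bone density and 19.38, so 20, for lean mass. A paired t calculation with the stated SD as SD of change gives 11 and 12. The mismatch of contrasts does not depend on which is right; 18 is used below as the number analysed.

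**Assumptions beyond the document.** Independent visit errors of equal variance σ², two-sided tests, and Bonferroni over three tests (0.05/3 = 0.0167). Changes are in units of the SD of a T1-T2 change. 40,000 simulated trials per scenario.

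**1. Same true change of 0.45 SD in both phases.** The program phase does not exceed the control phase. The pattern of T0-T1 not significant with T1-T2 significant appears in 23% of trials. The direct contrast, tested at 0.05, favours the program in about 2.5%, its nominal one-direction rate. This result needs no argument about phase length.

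**2. Steady drift, no program effect.** Drift in proportion to time is four times as large over 16 weeks as over 4.

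| Assumed 16-week drift (SD) | 4-week drift (SD) | Pattern appears |
|---|---|---|
| 0.2 | 0.05 | 5% |
| 0.3 | 0.075 | 11% |
| 0.6 | 0.15 | 47% |
| 0.9 | 0.225 | 82% |

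The raw direct contrast at 0.05 still favours the program in 18% of trials at a drift of 0.6 and in about 34% at 0.9. It lowers the rate but does not remove steady drift.

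**3. Retention.** With a true gain of 0.9 SD and half of it lost by T3, T2 vs T3 is non-significant in 74% of trials. With all of it lost, it is non-significant in 14%.

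**4. Cost of the direct contrast.** (T2-T1) - (T1-T0) = T2 - 2T1 + T0, with variance (1 + 4 + 1)σ² = 6σ² against 2σ² for T2-T1, so the standard error is √3 ≈ 1.7 times as large. Replacing T2 by T3 gives the same 6σ².
- Lean mass: 0.90/√3 = 0.52. Power at n = 18 is 55% at 0.05 and 35% at 0.0167, against 95% and 86% for T1 vs T2. 80% power at 0.05 needs 32 participants.
- Bone density: 59% and 39%, against 96% and 90%; 29 participants.
- If the two changes correlate at -0.5 (as implied above), 0 or +0.5, the number for 80% power is 32, 22 or 12 (lean mass) and 29, 20 or 11 (bone density).

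**5. Duration-scaled contrast.** (T2-T1) - 4(T1-T0) = T2 - 5T1 + 4T0, with variance (1 + 25 + 16)σ² = 42σ², 21 times that of T2-T1. It removes steady drift but has about 12% power at n = 18.

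**The case against.** The strongest reply is that the list is not closed. The protocol says the comparisons will follow the hypothesis and gives the three pairs as a special interest, and an analysis plan not shown here may define more. That stands, and it limits the point to the contrasts that are named. A reader might infer that the study has no analysis able to test Hypothesis 1; the document does not support that. It does single out three contrasts, and they are not the ones its hypothesis needs.

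A second reply is that the minimal detectable change already uses the control phase. It is a real descriptive safeguard, but it is a threshold for an individual's change. It does not test the mean program change against the mean control-phase change.

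A third is that drift should be small. Recruits are chronic and stable, are asked to keep their activity constant, and belong to a population in which the Introduction describes worsening over time. A drift of 0.9 SD would equal the whole planned lean-mass effect. This stands as a caution: the larger percentages rest on large assumed drifts. On the other side, the challenges section has vitamin D3 supplied at T0 to those not already taking it and diet instruction for everyone, so some change starting with the control phase is possible. The 23% result does not depend on drift over time.

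Two stronger readings should be set aside. A reader might suppose that a non-significant T2 vs T3 will be reported as benefit kept, or that the significant/non-significant pattern is the success criterion; the protocol states neither rule. Nor does the fourfold argument extend to practice effects, which follow repeat testing, and each phase contains one retest.

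**Conclusion.** The point holds in this form: the three comparisons named for Hypothesis 1 do not match it. None compares the program change with the control-phase change, and none compares T3 with a pre-program value. This follows from the text alone.

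The size depends on assumptions. With equal true change of 0.45 SD in both phases, the named tests give the misleading pattern in 23% of trials. Under steady drift the figure runs from 5% at 0.2 SD to 82% at 0.9 SD, and the document gives no basis for choosing a value. The 74% for T2 vs T3 shows how little that test says about T3 relative to T1; it is not the error rate of a rule in the protocol. All of these rest on 18 participants, independent visit errors and tests at 0.05/3.

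**What to change.** For outcomes measured at all four visits, name three planned contrasts for the Bonferroni family:
- T1 vs T2;
- (T2-T1) minus (T1-T0);
- (T3-T1) minus (T1-T0), with T1 vs T3 reported beside it. T1 vs T3 alone is not enough, because it again tests one change against zero.

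For non-normal outcomes, apply a signed-rank test to the same within-person differences. Report T0-T1 and T2-T3 as estimates with 95% confidence intervals. Because the phases last 4 and 16 weeks, add (T2-T1) minus 4 × (T1-T0) as a sensitivity estimate with its interval. It is too imprecise to serve as a test here.

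State that an excess over the control phase will be claimed only from the direct contrasts. Respiratory gas analysis is taken only at T1 and T2, so make no such claim for it.

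The change uses data already collected and keeps three tests. Its price is that the claim is harder to reach: about 55% power at 0.05, or 35% at 0.0167, for a true 0.9-SD effect at n = 18. The protocol should say so. Low power is a reason to limit the claim, not to infer it from separate tests.

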
### Potential Challenges and Appropriate Mitigation Strategies

A few potential challenges merit attention:

Some potential participants will have insufficient passive range of motion at the lower extremities to engage with the project. These participants will be provided with a 4- to 6-week home-based stretching program, will be reassessed, and may become eligible later.Female WU_SCI_ may be underrepresented. Efforts will be made for the sample to be representative of the SCI population and to have women make up 20% of the sample. However, since the minority of individuals affected by SCIs are female and the sample size is limited (n=20), it is unlikely that statistical analysis by subgroups (ie, male vs female) will be feasible in order to account for potential sex and gender differences. Nonetheless, descriptive statistics will present results separately for women and men whenever indicated.A small number of participants may demonstrate vitamin D deficiencies [102]. To mitigate this risk, at T_0_, the equivalent of 1 year of vitamin D3 supplementation will be provided to all participants who are not currently taking supplements. Moreover, all participants will be instructed on healthy balanced diets.Some participants may concurrently engage in extraneous physical activity or may seek cointerventions during the project. Participants will be asked to maintain their customary level of physical activity during the project and to avoid engaging in new cointerventions. Any unintended intervention (ie, contamination or cointervention) that may influence the results will be documented and its effect carefully verified by the research team and possibly considered as a dichotomous variable (ie, present vs absent).Some participants may experience some lower extremity neurorecovery. In the event a participant was to experience neurorecovery (ie, lower extremity motor score of ≥20 on the American Spinal Injury Association Impairment Scale), he or she would be withdrawn from the project and referred for a comprehensive neurological assessment and to an advanced locomotor training program.

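### Missing visits are filled with the group mean, which discards a participant's own earlier values and gives wrong standard errors for within-person change

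*Protocol article*

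**What the plan says.** In the protocol article, Quantitative and Qualitative Analyses, Hypothesis 1 is tested by repeated-measures analysis of variance or Friedman tests with Bonferroni-corrected planned comparisons, "with a special interest for the preintervention (T_0_ vs T_1_), intervention (T_1_ vs T_2_), and retention (T_2_ vs T_3_) phases". Under an intention-to-treat label, "all participants will be included in the final analyses, regardless of withdrawal, compliance, or unintentional missing data". The missing-data rule follows: "For missing data, imputation of the mean value for the specific group at the specific assessment time will be used". The section names no other method for missing data. The only other analysis set is an exploratory per-protocol one.

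Study Design describes "A prospective, longitudinal, self-controlled interventional study with multiple discrete measurement times", with no separate comparison group. The section on the walking program assigns participants to three training regimes by hip T-score, and these are the only groups that the rule could otherwise mean. Under Potential Challenges and Appropriate Mitigation Strategies, a participant with neurorecovery is taken out: "he or she would be withdrawn from the project and referred for a comprehensive neurological assessment".

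**The concern.** All evidence on Hypothesis 1 comes from comparing each person with himself or herself. Such a comparison is precise because stable differences between people cancel. The rule breaks this for anyone with a missing visit, whose change becomes other people's average minus his or her own baseline. Between-person spread enters a within-person contrast, and the test counts the filled value as real information. If the group means a training regime, the mean rests on fewer people and the defect is the same.

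At stake are the standard error and P value of the T1–T2 and T2–T3 contrasts and, if dropout is selective, the size of the gain. Filled T2 values would also enter the percent changes for Hypotheses 2 and 3 if the rule is applied there.

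**Working it through.** **Inputs.** From Sample Size Estimation: tibial bone density 466 to 532 ±70 (difference 66), leg lean mass 14.0 to 15.8 ±2 (difference 1.8), 18 evaluable, 20 in total, dropout 7.1%. From the analysis section: level 5%, taken as two-sided. Assumed, because the article gives neither: the T1–T2 correlation ρ and the dropout mechanism.

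**1. The plan's own figure.** The article says "a total of 18 participants are required to have an 80% chance of detecting" the stated increases. The formula for two independent means, 2 × (1.96 + 0.84)² × (SD/difference)², gives 2 × 7.85 × (70/66)² = 17.7, so 18, for bone density. For lean mass it gives 2 × 7.85 × (2/1.8)² = 19.4, so 20. A paired t-test with 70 as the SD of change needs only 11. Equivalently, 18 pairs at 66/70 = 0.94 SD of change have 96% power, so 96% is the comparator below. That mismatch is a separate matter. Dropout: 18/(1 − 0.071) = 19.4, so 20. Expected missing: 0.071 × 20 = 1.4, so 2 is used here.

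**2. One participant.** The assigned change is the observed T2 mean minus own T1. Someone one between-person SD below the mean at T1 is given the average gain plus 1 SD. Someone one SD above is given the average gain minus 1 SD. Neither change was observed.

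**3. Standard error, random dropout** (n = 20, k = 2, units of between-person SD). Mean imputation estimates (T2 mean of 18) − (T1 mean of 20), with variance 1/18 + 1/20 − 2ρ/20. The 18 observed pairs have variance 2(1 − ρ)/18. The reported standard error is from simulation.

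| ρ | True SE, imputed | Reported SE, imputed | True SE, 18 pairs |
|---|---|---|---|
| 0.50 | 0.236 | 0.224 | 0.236 |
| 0.90 | 0.125 | 0.119 | 0.105 |
| 0.95 | 0.103 | 0.099 | 0.075 |

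The reported error is about 4–5% too small. At high correlation the true error is also 18% (ρ = 0.90) to 38% (ρ = 0.95) larger than that of the observed pairs.

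**4. Error rates, random dropout** (100,000 simulated trials per setting, bivariate normal T1 and T2, paired t-test, unadjusted 5%).

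| ρ | Type I, imputed | Type I, pairs | Power at 0.94 SD of change, imputed | Power, pairs |
|---|---|---|---|---|
| 0.50 | 6.1% | 5.0% | 97% | 96% |
| 0.90 | 5.4% | 4.9% | 90% | 96% |
| 0.95 | 4.7% | 5.0% | 82% | 96% |

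**5. Bias.** Let dropouts start δ SD below the overall T1 mean. The stayers then lie 2δ/18 above it and carry ρ of that to T2, so the bias is ρ × δ/9.
- δ = 0: no bias.
- δ = 1: 0.10 (ρ = 0.90) and 0.11 (ρ = 0.95).
- δ = 1.2, ρ = 0.90: 0.12. δ = 1.3, ρ = 0.95: 0.14.

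Simulation with δ = 1.29 gave +0.130 and +0.137, against −0.014 and −0.007 for observed pairs. At ρ = 0.90 the reported standard error was then too large (0.145 against 0.117), so the harm shows in the estimate more than in false positives. If dropouts start higher than average, the sign reverses.

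**The case against.** The strongest defence is that little will go wrong at the dropout expected. One or two missing of 20 is the plan's own allowance, and attendance in the feasibility study was 97.7%. If those few are missing at random, the mean change is unbiased and type I error stays within about 5–6%. At ρ = 0.5 the filled analysis even rejects slightly more often than the observed pairs, and on the plan's effect power stays above 80% in every setting shown. All of this stands, and it limits the severity.

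It also stands that no simple replacement handles dropout of poor responders. In simulation with that mechanism (ρ = 0.95, 2 missing), the bias was +0.025 SD under mean imputation and +0.050 SD for an estimate conditioned on the person's own T1.

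Three stronger readings are tempting, and the article does not support them.
- **That the rule always biases the gain.** It does so only if dropout relates to baseline or response. The neurorecovery withdrawal makes some informative dropout possible. However, the article describes participants as having a very poor prognosis for walking recovery, and it does not suggest more than an occasional case.
- **That power falls from 80% to between 60% and 70%.** That needs an effect of about 0.7 SD of change, which the plan does not contain.
- **That the bias can be put in mg/cm³ by multiplying by 70.** That treats 70 as the between-person SD. At ρ = 0.90 the planned 66 would then be about 2.1 SD of change, and power would be close to 100% with or without imputation.

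**Conclusion.** The rule is wrong as written for a within-person analysis, and it is fixed in the article rather than left to an analysis plan. Its harm at the planned dropout is moderate and conditional, so this is a should-fix.

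Even under random dropout the standard error does not match the true variability. The consequence is a slightly raised type I error (about 6% at ρ = 0.5), or lost power for very stable outcomes (about 6 points at ρ = 0.90 and 15 at ρ = 0.95). An overstatement of about 0.12–0.14 between-person SD requires 2 dropouts who start about 1.2–1.3 SD low, which nothing in the article predicts. All figures rest on the assumed correlations, 2 missing values at T2, normality and an unadjusted 5% test. The Bonferroni correction would change the levels but not the defect.

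**What to change.** Delete the group-mean imputation. For continuous outcomes, fit a linear mixed model over T0–T3 to all observed values, with time as a factor, a within-participant covariance structure, REML and small-sample degrees of freedom. Take the Bonferroni-corrected planned contrasts from it. For ordinal or non-normal outcomes, use paired tests such as the Wilcoxon signed-rank test on observed pairs. State that all available data are used under a missing-at-random assumption, and that this does not remove bias if poor responders drop out.

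The cost is a rewritten paragraph and slightly more analysis work; the named software can fit the model. Participants with no follow-up will contribute only the visits they attended.

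Continued assessment of withdrawn participants is not part of this change, since it would add visits and scans. The statement that everyone is analysed regardless of withdrawal and the rule that some participants leave the project altogether need to be reconciled by the investigators.
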